### Participants

Children from Malletts Bay School in grades 3rd, 4th, and 5th grade and ranging in age from 7 to 11 years will be recruited. An IRB approved consent form, group information form, as well as an introduction to the study letter will be sent home with each student. The letter will provide instructions as to how each interested student (along with a parent/legal guardian signature) should complete the consent form and group information form. Students will return their signed consent form along with a completed group information form to their teacher. Study staff will collect and review completed consent forms from the teachers.

Children will indicate on the group information form (included with the consent form) the group (A or B) they would like to participate (Table 1). The investigators will randomize the children to either Group A or Group B on a first-come, first-served basis. Once the maximum capacity for any one group (n = 50) is reached, children will be randomized to the other group if they have indicated their willingness to participate in the other group. Or if the preferred group is at maximum capacity and the child did not request to participate in the other group, then the child would be notified in writing that the requested group was no longer available.

**Table 1 T1:** Group Stratification

**Group A**	Week 0	Physical Activity Program	Week 12
	tests and measures	3 days/week	tests and measures
**Group B**	Week 0	No Physical Activity Program	Week 12
	tests and measures		tests and measures

Once the consent form is received by the study staff, children and parents will be notified through letters mailed to their home address as to what group their child will be participating. The parent(s) of the child will then be contacted by phone to schedule the first testing session.

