### Assessments

All participant baseline measures will be performed 1–2 weeks prior to the first physical activity session. Follow-up measures will be performed within 1 week following the final physical activity session. For both Group A and Group B, the testing and measurement sessions will be scheduled at a convenient time before or after school and will be performed in a private room at the school. At the two testing and measurement visits, study staff will obtain weight, height, waist, hip and neck circumferences, resting heart rate and blood pressure for each enrolled child. Children will be asked to complete several questionnaires at both baseline and follow-up regarding their physical activity, eating habits, feelings and emotions, and quality of life. These measurements and questionnaires are expected to take approximately 15–20 minutes. Parent(s) will also be asked to complete questionnaires before and after the physical activity program. The parent questionnaires will include information regarding their education level, their child’s physical activity, eating habits, medications, illnesses, family history and quality of life. These questionnaires will be directly mailed to the parents and will include a postage-paid return envelope. We will also be asking teachers of enrolled participants to complete a brief questionnaire regarding the child’s classroom behavior before and after the physical activity program.

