#### Academic performance

Academic performance will be assessed through several methods including grades, achievement test scores, and curriculum-based measures (progress monitoring). The curriculum-based measures are a unique method as these are sensitive to and are validated to monitor progress compared to curriculum-based assessments. Curriculum-based assessments are often lengthy, not administered on a regular basis, and compare student scores to national samples. Curriculum-based measures are easy to administer, can be given as often as wanted/needed, and provide immediate feedback. Progress monitoring with curriculum-based measures focuses on individualized decision making in general and special education with respect to academic skill development at the elementary grades. Progress monitoring can be conducted frequently and is designed to estimate rates of improvement [8].

The proposed study will be utilizing two curriculum based measures developed by Pearson based on the work by Fuchs and Fuchs. The first is the M-COMP, which measures progress in basic number operations (addition, subtraction, multiplication, division) through grade 8. The second measure is the Oral Fluency Measure which measures progress in comprehension, reading, vocabulary, phonics etc. Criterion and norm based reference points are available. The norms are established through an aggregate score of the students in U.S. using the Pearson measures [8]. The curriculum-based measures will be performed 1–2 weeks prior to the first physical activity session. Follow-up measures will be performed within 1 week following the final physical activity session.

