#### Data analysis

All statistical procedures will be performed in SPSS, version 18.0. Significance will be set at the 0.05 level. Descriptive statistics including means and standard deviations will be computed for all of the data. Differences among the groups at Week 0 and Week 12 will be assessed by using Student’s independent *t*-test. Furthermore to account for baseline differences, a general linear mixed-model analysis of variance will be performed. A power analysis was performed to determine the sample size needed to determine significant pre- and post-differences in each group. With the alpha level set at 0.05, an anticipated effect size of 0.8, and the statistical power level set at 0.8, the minimum total required sample size was 8 participants. A power analysis was performed to determine the sample size needed to determine significant differences between Group A and Group B with a one-tailed *t*-test. With the alpha level set at 0.05, an anticipated effect size of 0.8, and the statistical power level set at 0.8, the minimum total required sample size was 42, with a minimum sample size per group of 21 participants. Therefore, with the planned total of 100 participants in this study, 50 of which will be assigned to Group A and 50 assigned to Group B, the minimum sample size required for analyses will be achieved.

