## Discussion

The proposed study described in this paper is the first to the authors’ knowledge to examine the effect of an unstructured, moderate to vigorous, before-school physical activity program on academic performance, classroom behavior, emotions, and other health related measures in elementary school-aged children. The results of this study will provide evidence to support the feasibility and efficacy of an unstructured, moderate to vigorous, before-school physical activity program in children. The unstructured physical activity with limited equipment, yet moderate to vigorous intensity design would allow others to easily and affordably replicate. Often, the initiation of novel physical activity programs is often viewed as cost-prohibitive and labor intensive. The design, setting, and population, however, may be replicated in relatively any elementary school with limited supplies and with a limited budget. Furthermore, the proposed study will provide insight regarding the ideal physical activity intensity and duration necessary to achieve a positive increase in academic performance.

The current study allows the participants to select and/or indicate their preferred group- Group A, tests and measures with the physical activity intervention or Group B, tests and measures only. This randomization design may be considered a limitation of the study; however, differences within each group, treatment and control will be assessed in addition to comparisons between the two groups. These within-group analyses will allow evaluation of the outcomes attributable to the physical activity intervention rather than attitudinal variables that may have been introduced with the self-selection of the groups.

The findings of this study will provide valuable information for other research groups looking to increase physical activity levels of children via school-based interventions. Furthermore, it will ascertain whether an unstructured, moderate to vigorous, before-school physical activity program is an effective method for future large-scale implementation.

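### Within-group pre-post analyses cannot separate the program's effect from self-selection, yet the plan rests attribution on them

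*Protocol article*

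**What the plan says.** **Allocation.** The protocol article, under Participants, says: "The investigators will randomize the children to either Group A or Group B on a first-come, first-served basis". Despite the verb, families name a group on a form, and places are filled in order of return up to 50 per group. The Discussion confirms it: "The current study allows the participants to select and/or indicate their preferred group".

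**The stated remedy.** After conceding that this may be a limitation, the Discussion says that "differences within each group, treatment and control will be assessed in addition to comparisons between the two groups". It then draws the conclusion at issue: "These within-group analyses will allow evaluation of the outcomes attributable to the physical activity intervention rather than attitudinal variables".

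**The analyses.** Data analysis contains a separate power calculation for "significant pre- and post-differences in each group", giving a minimum of 8 participants. It also plans independent t-tests between groups at Week 0 and Week 12, a one-tailed between-group power calculation (42 in total, 21 per group), and a general linear mixed-model analysis of variance to account for baseline differences.

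**The outcomes.** On timing, Assessments says: "All participant baseline measures will be performed 1–2 weeks prior to the first physical activity session". Follow-up comes within a week of the last session. Academic outcomes include curriculum-based progress monitoring, which "is designed to estimate rates of improvement". Weight, height and circumferences are taken in children aged 7 to 11.

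**The concern.** The article names its main threat to validity, self-selection, and offers one analytic answer to it. That answer does not work.

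A pre-post change in Group A is the program's effect plus everything else that moves the outcome over the same weeks. For the academic measures, improvement under ordinary teaching is what the instruments are built to detect. Children also grow, seasons change, and repeat testing and regression to the mean can shift scores.

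Nor does within-child comparison deal with attitude. It cancels a stable difference in level, such as a child who always reads better. It does not cancel a difference in trajectory, such as a motivated child who would have improved faster anyway.

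At stake is the main conclusion. The Discussion says the study will establish whether the program is effective enough for large-scale use. If a significant Group A change is read as the article invites, a program that does nothing could be credited with a gain in reading or mathematics.

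**Working it through.** **1. The plan's own figures.** For the between-group test (effect size 0.8, one-sided 0.05, power 0.8), the exact noncentral-t calculation gives 21 per group, 42 in total, with power 0.817. This reproduces the article. For the within-group test, a paired t-test with 0.8 on the change-score scale needs 12 children one-sided or 15 two-sided. The stated 8 can be reached only with inputs that the article does not give, for example 0.8 on the raw SD with a pre-post correlation of about 0.67 to 0.72 (one-sided). So 8 cannot be verified, but it is not shown to be wrong, and nothing below depends on it.

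**2. What each quantity contains.** Let P be the program effect, T the time effects common to both groups (teaching, growth, season, retest), and S_A and S_B the extra change specific to children who chose A or B.
- Change in A = P + T + S_A
- Change in B = T + S_B
- Change in A minus change in B = P + (S_A − S_B)

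The within-group change in A isolates P only if T and S_A are both zero. The between-group difference in change removes T and leaves S_A − S_B. Neither removes selection.

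**3. How far T alone can carry the within-group test.**
- From the article: n = 50 per group and alpha 0.05.
- Assumed, because the article gives no natural gain and no SD of change: a gain g of 0.2 to 0.8 SD of the change score, P = 0 and S_A = S_B = 0.
- Rejection probability of the paired t-test: noncentral t with 49 degrees of freedom and noncentrality g × √50, where √50 = 7.07.
- The sidedness of the within-group test is not stated, so both are shown.
- The last column is from a simulation with 20,000 replicates.

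| g | g × 7.07 | Group A test significant, two-sided | one-sided | Between-group test of change, two-sided |
|---|---|---|---|---|
| 0.2 | 1.41 | 28% | 40% | 5.4% |
| 0.3 | 2.12 | 55% | 67% | 5.0% |
| 0.5 | 3.54 | 93% | 97% | 4.9% |
| 0.8 | 5.66 | ~100% | ~100% | 4.7% |

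**4. Adding self-selection.** Again P = 0, two-sided 0.05 and 50 per group, but now the children who chose A gain more. All gains are assumed, in SD of the change score.

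| Gain in A | Gain in B | Group A pre-post test significant | Between-group test of change significant |
|---|---|---|---|
| 0.4 | 0.2 | 79% | 17% |
| 0.5 | 0.2 | 93% | 32% |
| 0.6 | 0.2 | 99% | 51% |

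For the middle row, the between-group noncentrality is (0.5 − 0.2) × √(50/2) = 0.3 × 5 = 1.5. The between-group contrast is far less exposed than the within-group test, but it does not hold its nominal 5% when trajectories differ by choice of group.

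**The case against.** The strongest reply is that the within-group tests do not stand alone. The Discussion adds them to between-group comparisons, Group B has the same measures at the same times, and a mixed model is planned. Teaching and growth shared by the groups would show in Group B and largely cancel in a comparison of change. Nothing makes the Group A test the deciding one. This stands, and it rules out the reading that the plan will necessarily declare effects for an inert program. It does not rescue the sentence, which credits the within-group analyses, and not the between-group contrast, with separating intervention from attitude.

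A reader might also infer a rule that an effect is claimed when Group A's change is significant and Group B's is not. Such a rule would be invalid, but the article states none, so no error rate for it is counted here.

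Three smaller objections also stand:
- The article does not say that the same test form is reused, so practice on identical items is not established.
- For weight and circumferences, growth would more likely mask a favorable change than create one. The risk of false credit is clearest for the academic measures.
- Within-child comparison does remove stable differences in level, so it is not useless against self-selection, only insufficient.

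Finally, the sentence is interpretive and the limitation is disclosed. That makes it easy to correct. But the pre-post tests are separately powered, so this is more than loose wording.

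**Conclusion.** The concern holds for the attribution claim. Within-group change cannot show what is attributable to the program rather than to self-selection, because it contains both common time effects and any trajectory particular to children who chose the program. This follows from the structure of the comparison and needs no numerical assumption.

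The percentages do need assumptions. They rest on gains that the article does not give, on 50 children per group, on normally distributed change scores and on a zero program effect. They show how easily a paired test turns significant without a program effect; they do not forecast this trial's error rate.

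The documents do not support the stronger inference that the whole plan must credit schooling and growth to the program, since between-group analyses are also planned. Nor do they support treating the between-group difference in change as free of bias. It removes common time effects only, and with assumed gains of 0.5 against 0.2 SD from self-selection alone it still rejects in about 32% of trials.

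**What to change.** 1. Delete the Discussion sentence that attributes within-group results to the intervention.
2. State that the effect estimate is the between-group difference in change from Week 0 to Week 12, with its 95% confidence interval. It can be the group-by-time contrast of the planned mixed model or a baseline-adjusted difference. The article does not name the contrast, so it should be written down.
3. Report within-group changes descriptively, and drop pre-post significance in each group as a powered objective.
4. State that groups are formed by preference and are not randomized. Say that the between-group contrast removes only time effects common to both groups and remains open to confounding by self-selection, and limit causal claims to match.

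**Cost.** Data collection, sample size and conduct do not change. The edits are to the Discussion, the analysis and power statements, and the description of allocation. The price is that within-group p-values no longer support efficacy claims and the conclusion becomes more cautious.
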